### Study product and intervention

3.6

The study products, including active (probiotics) sachets and placebo sachets, are provided by Lallemand S.A.S., Blagnac, France. Each active (probiotics) sachet is 1.5 g, containing 1.425 × 10^8^ colony-forming units (CFU) of *Bifidobacterium infantis* R0033, 1.425 × 10^8^ CFU of *Bifidobacterium bifidum* R0071, and 9.6 × 10^9^ CFU of *Lactobacillus helveticus* R0052. Under refrigeration, the probiotics sachet is stable for 6 months at 2 to 4°C. The placebo sachet is made with 3% magnesium stearate and 97% potato starch, identically packaged and stored, and has the same appearance, color, and taste as the probiotics sachet. One sachet per day will be dissolved in the first feeding bottle of the day and then will be administered orally to participants by their parents or guardians for 4 weeks. If the participant vomits after taking the drug, no additional dose will be given. The volume of milk of the first feeding bottle actually drunk will be recorded in the case report forms (CRFs). The study products will be directly provided to parents according to the randomization list at the second visit (V2) in sufficient quantity for 28 days, as 28 sachets.

### Study procedure and clinic schedule

3.7

Participants will be required to pursue a 2-week run-in, 4-week intervention, and 8-week follow-up period. The duration of subjects’ participation will be 14 weeks, with total 5 visits: inclusion (Visit 1, Day 1), start of intervention (V2, D15), end of intervention (V3, D44), and follow-up (V4 and V5, D72 and D100) (Figs. 1 and 2).

**Figure 1 F1:**
[figure not shown]
Flowchart of the trial.

**Figure 2 F2:**
[figure not shown]
Clinic schedule of the trial.

During the first visit (V1), a face-to-face interview will be conducted with the participant's parents. An investigator (pediatrician) will explain the study procedures in detail, particularly the purpose of the study, the procedures to be undergone, and the potential risks and benefits of participation. The inclusion and exclusion criteria will be reviewed to determine if the participant qualifies for the study. If the parents agree to have their infant enrolled in the trial, one of them will sign an informed consent. At the same time, the investigator will collect relevant information on demography, medical history, and concomitant medications.

During this first visit, parents can choose any brand of milk powder in the list of allowed infant formulas (without probiotics; if with prebiotics, GOS < 2 g/100 g and no FOS inside) presented by the investigators. The investigators will recommend the Biostime Infant Formula (Biostime Inc., Guangzhou, China). If parents are willing to choose the Biostime Infant Formula from the list, they will be provided a free and sufficient supply of the Biostime Infant Formula. The infant's feeding will have to be completely switched to the new infant formula within 1 week (D1-D8).

A saliva sample will be obtained at the site by the investigators at V1 (D1), V2 (D15), and V3 (D44). Parents will be instructed to collect a stool sample of their infant at home at V1 (before starting the new infant formula), V2 (within 24 h before the visit time), and V3.

The infant's diaries will be provided to parents at each visit, and they will be instructed to fill in these diaries daily from D8 to D99 in order to record GI symptoms (Bekkali scale),^[22]^ crying episodes (number and duration), number of stools, compliance (volume of milk of the first feeding bottle actually drunk, planned to be drunk, and regurgitated), and potential concomitant medications. Moreover, a physical examination will be conducted at each visit, and potential adverse events (AEs) will be monitored throughout the trial by the investigators.

### Stool collection and bacteriological examination

3.8

Fresh stool samples will be collected in plastic bags, maintained anaerobically, and then sent to the lab for analysis. Stool samples (0.5 g) will be then mixed in 5 mL of sterile Ringer's solution containing 5% cysteine, allowed to vortex for 5 to 10 minutes, and shifted the supernatant for geometric dilution in a reagent bottle in sterile conditions.

Various media will be used for the selective isolation of different microorganisms: freshly prepared Man, Ragosa, and Sharpe (MRS) agar to which Mupirocin lithium salt is added, for *Bifidobacteria*; LBS agar supplemented with 1 mL/1000 mL of Tween 80 and 1.3 mL/1000 mL of glacial acetic acid, for *Lactobacilli*; TSC agar to which 0.8 mL/100 mL of 5% D-cycloserine is added, for *Clostridium perfringens*; modified GAM agar, to which 80 μg/mL of vancomycin, 1 μg/mL of kanamycin, 0.01 mL/100 mL of 1% vitamin K1, 0.25 g/100 mL of hemin, and 7 mL/100 mL of blood are added, for *Bacteroides*; bile esculin azide (BEA) agar, for *Enterococci*; and violet red bile dextrose (VRBD) agar, for *Enterobacteria*.

The seeded, streaked culture plates will be placed in anaerobic containers to maintain anaerobic conditions and then will be incubated at 37°C. Each anaerobic container contains a resazurin oxygen reduction indicator to ensure *anaerobicity* during incubation. The MRS, LBS, and modified GAM plates will be incubated anaerobically for 48 hours; the BEA, TSC, and VRBD agar plates will be incubated anaerobically for 24 hours. Colony counts will be done manually and expressed as CFU/g; numbers over 300 will be designated as too numerous to count (TNTC).

After incubation, colonies with representative morphology and color typical of specific species will be randomly selected and identified with the microorganism MASS system for confirmation.

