### Primary analysis

2.2

The primary endpoints, the V2-V3 changes in *Bifidobacterium bifidum*, *Bifidobacterium longum ssp. infantis*, *Lactobacillus helveticus*, *Clostridium perfringens*, *Enterococcus*, *Enterobacteria*, and *Bacteroides* in stools will be analyzed using the following ANCOVA model (SAS PROC MIXED):

*Y* = Product +Baseline + (Product × Baseline)

where

Y = V2–V3 change in fecal microbiota

Product = study products

Baseline = baseline value (V2)

Product × Baseline = Product − Baseline interaction

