### Secondary analysis

2.3

The above-mentioned ANCOVA model will be conducted for analysis of the V2–V3 change in salivary SIgA levels.

A within-group analysis to compare V2 and V3 values (e.g., fecal microbiota and salivary SIgA) will be conducted in each product group using a paired Student's *t*-test or a Wilcoxon signed-rank test, depending on the condition of application of the statistical test.

The outcomes related to GI symptoms and well-being (weekly average number of stools, stool form, amount of stools, color of stools, number of crying incidents, and duration of crying) will be analyzed using the following ANOVA model for repeated measurements (subject will be considered as a random effect, using SAS PROC MIXED):

Y = Product + Week + (Product × Week)

where Y = study endpoint at Wr (D8 to D15), W1 (D16 to D22), W2 (D23 to D29), W3 (D30 to D36), or W4 (D37 to D43)

Product = study products

Week = W1 to W4 weeks (between V2 and V3 visits)

Product × Week = interaction between the product and the week

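### As written, the primary ANCOVA is fitted to arithmetic changes in CFU/g, with no log10 scale or rank-based fallback and no rule for plates too numerous to count

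*Protocol article*

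**What the plan says.** Section 3.8 (stool collection and bacteriological examination) describes selective plating after a dilution step: "shifted the supernatant for geometric dilution in a reagent bottle in sterile conditions". For the result it says: "Colony counts will be done manually and expressed as CFU/g; numbers over 300 will be designated as too numerous to count (TNTC". It does not give the number of dilutions or say which plate supplies the count. It also does not say what value stands in for an uncountable or empty plate.

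Section 3.12 makes the V3 (D44) minus V2 (D15) changes in seven organisms the primary endpoints. Section 2.2 says these "will be analyzed using the following ANCOVA model (SAS PROC MIXED"), with terms for Product, Baseline (the V2 value) and Product × Baseline, and with "Y = V2–V3 change in fecal microbiota". Neither section names a transformation.

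Nonparametric options do appear elsewhere. Section 2.1 allows a Mann–Whitney test for baseline characteristics. Section 2.3 allows, for within-group V2 to V3 comparisons only, a "Wilcoxon signed-rank test, depending on the condition of application of the statistical test". For saliva, section 2.3 adds: "The above-mentioned ANCOVA model will be conducted for analysis of the V2–V3 change in salivary SIgA levels".

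Section 3.2 explains that 100 per group comes from a recommended minimum of 50 plus an allowance for drop-out, not from a power calculation. The article therefore contains no SD, effect size or power.

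**The concern.** Counts read from serial dilutions usually vary multiplicatively between infants. On such data an arithmetic difference in CFU/g is governed by the few samples with the highest counts. The residuals are then neither normal nor of equal variance, and a t-type test of Product is unreliable. The Product × Baseline term makes this worse, because the same few infants also have high leverage on the two baseline slopes.

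At stake are the power and the false-positive rate of all seven primary comparisons. The article considered distributional fallbacks for baseline and within-group tests but provides none for the primary between-group test.

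A second, smaller question follows from the counting limit. A plate labelled too numerous to count has no number to subtract. If a sample has no countable plate and is then left out, the omission depends on the outcome itself.

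**Working it through.** **Figure to reproduce.** None. The article states no power, effect size or SD.

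**Inputs from the article.** 100 infants per arm (50 as the recommended minimum), alpha 0.05, ANCOVA of change on Product, Baseline and Product × Baseline, unit CFU/g.

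**Assumptions.** Two-sided test; log-normal counts with log10 SD s between 0.3 and 1.5; V2–V3 correlation 0.5 on the log scale; a constant shift d in log10 counts in the active arm; baseline centred when the interaction is fitted.

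**Why the raw scale is fragile.** For a log-normal count the coefficient of variation is √(exp[(s·ln 10)²] − 1). This gives
- s = 0.3: √(exp 0.477 − 1) ≈ 0.8
- s = 0.5: √(exp 1.325 − 1) ≈ 1.7
- s = 1.0: √(exp 5.302 − 1) ≈ 14
- s = 1.5: √(exp 11.93 − 1) ≈ 390

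**Shift that gives 80% power on log10.** d = (1.960 + 0.842) · s · √(1 − 0.5²) · √(2/n). With n = 100 this is 2.802 × 0.866 × 0.1414 × s = 0.343 s, so d = 0.103, 0.172, 0.343 and 0.515 for the four SDs. At s = 1.0, for example, that is a ratio of 10^0.343 ≈ 2.2.

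**Simulated power at that shift** (2,000 trials per setting, 100 per arm):

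| log10 SD | log10 scale | raw, no interaction | raw, with interaction | share of total sum of squares from the 5% most extreme changes (median) |
|---|---|---|---|---|
| 0.3 | 78% | 65% | 66% | 51% |
| 0.5 | 80% | 49% | 51% | 73% |
| 1.0 | 80% | 18% | 25% | 96% |
| 1.5 | 82% | 8% | 18% | 99% |

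A separate set of simulations of the stated model gave 66%, 52%, 26% and 17% for the interaction column. The two sets agree within simulation error: √(0.5 × 0.5/2000) ≈ 1.1 percentage points at 50%. With 50 per arm, and d recalculated, the interaction column is 68%, 51%, 28% and 20%.

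**Type I error on raw counts.** With the interaction term, 100 per arm and 1,000 null trials, it is 7.1% at SD 1.0 and 13.0% at SD 1.5. The separate set gave about 8–13% over that range. With 50 per arm it is 11.3% and 13.7%. Without the interaction it drops to about 2% at both SDs. So the higher power of the interaction model at large SD is partly a matter of rejecting too often. On log10 it stays between 5% and 6% throughout.

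**Large shift.** With d fixed at 0.5 log10 and 100 per arm, the interaction model on raw counts has 99.6% power at SD 0.5 (log10: 100%), but 41% at SD 1.0 (log10: 98%).

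**If samples without a countable plate were dropped.** Log10 analysis without interaction, SD 1.0, true shift 0.5, 100 per arm, with the limit placed at a percentile of the baseline distribution:

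| Limit | lost, placebo | lost, active | estimate if dropped | power if dropped | estimate if set to the limit | power if set to the limit |
|---|---|---|---|---|---|---|
| 95th | 8.7% | 15.4% | 0.40 | 92% | 0.46 | 98% |
| 90th | 16.7% | 26.4% | 0.36 | 86% | 0.43 | 97% |
| 80th | 31.4% | 43.5% | 0.31 | 70% | 0.36 | 96% |

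Full data give an estimate of 0.50 and 98% power. Dropping loses more infants from the arm with higher counts and pulls the estimate towards zero. Setting the value to the limit keeps nearly all the power but still shrinks the estimate.

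**The case against.** The strongest objection is that the article never says the ANCOVA uses untransformed counts. CFU/g is a laboratory reporting unit, section 2.2 names no scale for Y, and a log10 step could sit in an analysis plan that is not shown. The first part is right: the raw scale is an inference. But the article goes beyond silence. It fixes the unit, the subtraction, the procedure and every model term, and it gives distributional fallbacks for other tests. A log step elsewhere would change the Y defined here.

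Four stronger readings are tempting, and the documents do not support them.
- **That power collapses.** This depends on an SD the article does not give, and there is no stated power to fall from. At SD 0.3 the loss is moderate, and for a 0.5 log10 shift at SD 0.5 it is negligible.
- **That the highest counts will be lost.** A limit of 300 colonies reads most naturally as a limit per plate, and section 3.8 describes geometric dilution before plating. A sample with one uncountable plate may have a countable one at a higher dilution. Nothing says such samples are excluded.
- **That losing them would create an apparent benefit.** Under the assumptions used, dropping them attenuates a true increase.
- **That the SIgA analysis is shown to be faulty.** No spread for SIgA is given and no calculation was made for it.

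**Conclusion.** The point holds in this form: followed literally, sections 2.2, 3.8 and 3.12 lead to a normal-theory ANCOVA, with interaction, of arithmetic CFU/g changes, and no transformation or rank-based fallback is provided for it. If counts are roughly log-normal, this is an inferior analysis. The power lost, against about 80% on log10, ranges from about 14 points (80 to 66) at log10 SD 0.3 to about 63 points (80 to 17) at SD 1.5, with false-positive rates of about 8–13% at SDs of 1.0–1.5. Every one of these figures rests on assumed log-normality, a correlation of 0.5, the chosen SDs and the chosen shift. The direction is secure if the counts are markedly skewed; the size is not known from the article.

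The counting limit is a secondary point and a conditional one: it matters only for samples with no countable plate, and only if they are left without a value.

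**What to change.** In section 2.2, define Y as log10(V3 CFU/g) − log10(V2 CFU/g) and Baseline as log10(V2 CFU/g). Report the arm difference in log10 units and, back-transformed, as a geometric-mean ratio with its confidence interval.

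In section 3.8, state that the count is taken from a dilution with no more than 300 colonies. State also that a sample with only uncountable plates, or with no growth, is kept as right- or left-censored at the corresponding limit and never set to missing. No growth needs its own rule because the log of zero is undefined. A Tobit model or a rank-based comparison can serve as the sensitivity analysis. Modelling log10 V3 with log10 V2 as a covariate gives the same Product effect as modelling the change, and lets the V3 censoring enter directly.

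A log scale for SIgA in section 2.3 is worth considering on the same reasoning, as a suggestion only.

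The cost is a few lines of analysis wording and one rule on the laboratory worksheet, settled before unblinding so that the scale is not chosen with the results in view. The downsides are that results are read as ratios, not arithmetic differences, and that a Tobit model leans on the assumed shape of the tail.

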### Saliva collection and SIgA measurement

3.9

Infants will be allowed to chew or suck on the swab for 30 to 60 seconds, followed by mopping up any pooled saliva left in the mouth or on the face. The samples are then recovered immediately by compression in a syringe, and the procedure is repeated to collect more saliva if the initial amount is too small.

Saliva samples will be centrifuged at 13 000 × g for 5 minutes at room temperature, and then the supernatant is stored at −20°C. For the SIgA assay, the SIgA concentration is assessed by means of particle-enhanced immunonephelometry. Briefly, the saliva samples are processed at a 1:5 dilution (as recommended), and evaluation of SIgA is performed automatically in mg/L. Reference curves are generated by multi-point calibration. Serial dilutions of N IgA Standard (human) are automatically prepared by the instrument using N Diluent.

### Safety assessment

3.10

An adverse event (AE) has been defined as any unfavorable or unintended clinical or other occurrence during the study period that may or may not be causally related to the intervention. All AEs considered not, unlikely, possibly, probably, or definitely related to the test product will be recorded in the CRFs.

A serious AE is defined as event that is fatal, life-threatening, disabling, or incapacitating or results in hospitalization, a prolonged hospital stay, or malformation. All will be also recorded in the CRFs, whether they are related to the test product or not. Probiotics are generally considered safe and well tolerated, and any serious AEs that might be possibly, probably, or definitely related to the test product will be regarded as unexpected. All serious AEs will be reported as soon as possible to the national Food and Drug Administration (FDA) and local FDA, the sponsor, and Infant Hospital. Any serious AEs that might be related to the test product will immediately lead to the discontinuation of the test product, and the study subject will be followed until the conclusion of the event.

### Quality control

3.11

To maintain the accuracy and quality of the clinical trial, audits and monitoring will be implemented by the sponsor. Clinical research associates will regularly monitor whether the clinical trial is proceeding based on the protocol by checking trial master files, informed consent forms, CRFs, adverse events, and compliance with study productions.

### Study endpoint

3.12

The primary endpoints are the V2-V3 changes in composition of the fecal microbiota, including *Bifidobacterium bifidum*, *Bifidobacterium longum ssp. infantis*, *Lactobacillus helveticus*, *Clostridium perfringens*, *Enterococcus*, *Enterobacteria*, and *Bacteroides* (defined as V3 [D44]-V2 [D15]). The secondary endpoints are:♦the V2-V3 change in SIgA antibody levels in saliva samples♦GI symptoms and well-being, as recorded daily by parents in the infant diaries; the following outcomes will be calculated on a weekly basis:1.average daily number of stools; for each subject, the total number of stools per day will be recorded in a 7-day diary, and then the average daily number of stools will be calculated. (The same procedure will be applied for the following endpoints.)2.average daily Infant Stool Form scores consistency (4-point scale), average weekly amount (4-point scale, letters will be replaced by figures, i.e., “A” to “1,” “B” to “2,” etc.) and color (6 categories), using the validated scale for preterm and term infants proposed by Bekkali et al.^[22]^3.average daily number of crying episodes4.average daily duration of crying episodes.♦the changes in growth parameters such as weight, length, and head circumference♦the numbers of AEs and serious AEs

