## Abstract

The gastrointestinal (GI) tract of a fetus in utero is sterile but it becomes colonized with environmental microorganisms shortly after birth. Since the gut microbiota undergoes substantial changes in early life, healthy gut microflora is essential to an infant's gut health and immune system and probably also has an effect on overall health status in later life. Probiotics, defined as viable microbial preparations that have a beneficial effect on the health of the host, represent a rapidly expanding field. Although randomized controlled trials using probiotics in infants have shown promising results in the prevention and treatment of common diseases such as diarrhea and allergy, little is known about whether probiotics could offer benefits to healthy infants. We have designed a randomized controlled trial to test the hypothesis that an oral preparation of probiotics is superior to placebo in improving digestive and immune function in healthy infants.

The trial will be a randomized, double-blind, placebo-controlled, 2-parallel-group study in Shanghai, China. After a 2-week run-in period, 200 exclusively formula-fed healthy infants aged 4 to 6 months will be randomly allocated to receive either a probiotic product containing *Bifidobacterium infantis* R0033, *Bifidobacterium bifidum* R0071, and Lactobacillus helveticus R0052 or an identical placebo once daily for 4 weeks and will be followed up for 8 weeks. The duration of the subject's participation will be 14 weeks, with a total of 5 visits: inclusion (Visit 1, Day 1), start of intervention (V2, D15), end of intervention (V3, D44), and follow-up (V4 and V5, D72 and D100). Stool and saliva samples will be collected at the first 3 visits to measure microbial populations and secretory immunoglobulin A (SIgA), respectively. Physical examination will be performed at each visit, and tolerance records will be completed 1 day prior to each visit. The primary endpoints will be the changes in the composition of fecal microbiota, particularly the *Bifidobacterium bifidum* population. The secondary endpoints will include the change in salivary SIgA level, growth parameters, digestive tolerance, and adverse events.

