### Statistical analysis

2.1

Statistical analysis of all data will be performed by a specialized statistician in a blind manner. To estimate the efficacy of this trial, both the intention-to-treat and per-protocol populations will be analyzed. Baseline characteristics will be compared by unpaired Student's *t*-test (parametric test) or Mann–Whitney test (nonparametric test) and chi-square or Fisher's exact test (if one of the expected frequency < 5). All statistical analyses of the data will be performed using SAS software version 9.3 or higher (SAS Institute Inc., Cary, NC), and a *P*-value < 0.05 will be considered statistically significant. The target variables for analysis are as follows.

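### Seven co-equal primary endpoints are each judged at an unadjusted P < 0.05, in two populations with neither leading, so the superiority claim has no fixed error rate

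*Protocol article*

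**What the plan says.** All references are to the protocol article; no SAP is at hand.

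- **Endpoints.** Section 3.12 (Study endpoint) says "The primary endpoints are the V2-V3 changes in composition of the fecal microbiota, including" and lists seven organisms. Three match species in the active sachet (section 3.6): *B. bifidum*, *B. longum* ssp. *infantis* and *L. helveticus*. Four do not: *Bacteroides*, Enterobacteria, *Enterococcus* and *C. perfringens*. None is ranked above another.
- **Model.** Section 2.2 (Primary analysis) repeats the seven; their changes "in stools will be analyzed using the following ANCOVA model (SAS PROC MIXED").
- **Threshold.** Section 2.1 (Statistical analysis) sets one criterion for all analyses: a P-"value < 0.05 will be considered statistically significant". It is not divided across endpoints.
- **Populations.** The same section says that for efficacy "both the intention-to-treat and per-protocol populations will be analyzed". Neither is named as leading.
- **Emphasis.** The abstract says "The primary endpoints will be the changes in the composition of fecal microbiota, particularly the" *B. bifidum* population. Sections 2.2 and 3.12 do not carry this emphasis over.
- **Hypothesis.** The abstract sets out to test whether "an oral preparation of probiotics is superior to placebo in improving digestive and immune function in healthy infants".
- **Within-arm tests.** Section 2.3 (Secondary analysis) adds "A within-group analysis to compare V2 and V3 values" in each product group.

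**The concern.** The trial is framed as a test of superiority, but the article does not say which result would establish it. Seven between-arm tests all carry primary status, each is judged at the full 0.05, and each can be run in two populations. A reader following the text could call the trial positive on any one organism in either population. The false positive rate attached to that conclusion would then be well above the nominal 5%. The abstract's stress on *B. bifidum* could have settled the matter, but the sections that define the endpoints and the model leave it out. A lead endpoint or lead population chosen once results are known would not be credible, so the choice has to be made in advance.

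**Working it through.** The article gives no family-wise error rate, power or calculated sample size, so there is no stated figure to reproduce.

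**Inputs from the article.** Seven primary tests (sections 2.2 and 3.12); 0.05 per test and two populations (section 2.1); three of the seven organisms are of species administered in the sachet (section 3.6).

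**Assumptions, not in the article.** Any one significant organism counts as a positive primary result. Tests are two-sided; sidedness is not stated. Correlation between the test statistics is taken as equal for all pairs and varied from 0 to 0.8. Section 3.2 expects high drop-out but gives no rate, so per-protocol is taken as 90% to 50% of ITT.

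**Step 1: seven independent tests, one population, no true effect on any organism.**

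1 − 0.95^7 = 1 − 0.698 = 0.302, or 30.2%. Whatever the dependence, the sum of the levels gives an upper bound of 7 × 0.05 = 0.35.

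**Step 2: only the four non-administered organisms are null.**

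1 − 0.95^4 = 1 − 0.815 = 0.185, or 18.5% under independence. This matters because a null effect is least plausible for the organisms actually given.

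**Step 3: correlated tests, and either population counting.** Simulation with 400,000 draws and seven normal test statistics at equal pairwise correlation. Per-protocol is treated as a subset of ITT, so the two statistics for one organism correlate at the square root of the per-protocol fraction (√0.9 = 0.95; √0.5 = 0.71).

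| Pairwise correlation | One population | Either, per-protocol 90% of ITT | Either, per-protocol 50% of ITT |
|---|---|---|---|
| 0 | 30.2% | 37.4% | 45.5% |
| 0.2 | 28.7% | 35.6% | 43.5% |
| 0.3 | 27.1% | 33.7% | 41.4% |
| 0.5 | 23.0% | 28.6% | 35.4% |
| 0.8 | 14.8% | 18.6% | 23.3% |

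The lowest figure, 14.8%, is still about three times 5%.

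**Step 4: what adjustment across seven would cost.** The smallest P-value must fall below 0.05/7 = 0.0071. A test with 80% power at two-sided 0.05 has an expected statistic of 1.960 + 0.842 = 2.802. The critical value at 0.0071 is 2.690. Power becomes Φ(2.802 − 2.690) = Φ(0.112), about 54%.

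**The case against.** **A SAP may settle this.** The article condenses a fuller protocol, and multiplicity methods and the lead population are often set in a SAP. A threshold of 0.05 does not by itself exclude adjusted P-values. It is therefore right not to conclude that the trial has no error control anywhere. What remains is what the article itself fixes: seven equal primary endpoints and one undivided threshold for all analyses. If a SAP contains a multiplicity rule, this text still needs to be brought into line with it.

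**The success rule is assumed.** This stands. The inflation arises only if one significant organism is enough. If all seven had to be significant there would be none. The article states neither rule, so the percentages describe a reading that it permits, not one that it declares.

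**Planning both populations is ordinary practice.** Also true, and the article does not say that a result in either one suffices. The either-population figures apply only if it is read that way.

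**Stronger readings to avoid.** A reader might treat the 14 tests as independent and quote 1 − 0.95^14 = 51.2%. That is too high, because the per-protocol infants are a subset of the ITT infants; the table allows for this. A reader might also infer that the within-arm tests will be used to claim a product effect. The article labels them secondary and makes the between-product ANCOVA the primary analysis. If both arms share the same natural change and each within-arm test has power p, exactly one arm is significant with probability 2p(1 − p). That is 50% at p = 0.5, which is its maximum, 32% at 0.8 and 18% at 0.9. This is a reason for careful reporting, not evidence of a fault in the primary analysis.

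**Conclusion.** The concern holds for the primary endpoints as the article states them. Under an any-one-counts rule, in one population and with all seven nulls true, the chance of at least one false positive primary result is 30.2% under independence and about 29% to 15% at correlations of 0.2 to 0.8. With only the four non-administered organisms null it is 18.5% under independence. Letting either population count takes the seven-test figure to about 37–46% at zero correlation and 19–23% at 0.8.

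These figures rest on an assumed success rule, assumed correlations and an assumed per-protocol fraction. The underlying facts do not: the equal status of the seven endpoints, the undivided threshold and the two unranked populations are all in the text. The article's emphasis on *B. bifidum* in the abstract alone is an inconsistency that should be resolved in any case. The point bears on what counts as trial success and should be settled before unblinding.

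**What to change.** 1. **Endpoint.** Preferably name the V2–V3 change in *B. bifidum* as the single primary endpoint in sections 2.2 and 3.12, which agrees with the abstract, and make the other six organisms secondary with Holm adjustment. Alternatively keep all seven primary and apply Holm across them at a family-wise 0.05. Amend the blanket threshold in section 2.1 to match.
2. **Population.** State that ITT carries the primary test and per-protocol is supportive.
3. **Within-arm results (minor).** Report the V2–V3 changes in each arm as estimates with confidence intervals, and base any claim of a product effect only on the between-arm ANCOVA.

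**Cost.** The change is to the wording of the protocol and any SAP. The statistical price depends on the option. Holm has no preset order; its first step is the strictest. Across seven endpoints, a test that would have had 80% power at 0.05 has about 54% at that step. A single named primary endpoint is tested at the full 0.05 and loses nothing, while the other six give up primary status and bear the adjustment. No stated power figure is invalidated, because section 3.2 reports that no formal sample size calculation was made.
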